**Figure 1 figure1:**
[figure not shown]
Round 1 mock-up screenshot.

**Figure 2 figure2:**
[figure not shown]
Round 2 mock-up screenshot.

### Data Analysis

There are two types of data analysis that will be performed in this study. First, qualitative data from expert and EL participant interviews; feedback from pilot testers about EL; responses to all open-ended questions, rationale comments, and discussions within EL; and round-table discussions will be analyzed thematically by identifying and describing explicit and implicit ideas in the data. Applied thematic analysis [47] will be used because it helps reduce large amounts of textual data and present them in easy-to-understand statements that could be used to explain how experts feel about patient engagement in guideline development, how the EL system should be modified to facilitate patient engagement in care guideline development, how patient input should be solicited, and what participants think about an online approach to patient and caregiver engagement in guideline development once they participate in the study. To expedite the data analysis and ensure its usefulness, we will begin with a deductive approach to directly answer our research questions. At the same time, we will use an open coding strategy to flag interesting ideas and themes that may not be directly relevant to research questions but should be explored further once preliminary data analysis is complete or once more data have been analyzed [48]. Such an inductive approach is crucial for identifying unanticipated ideas and issues that frequently emerge from open-ended questions.

Given the volume of data collected from different types of participants, we will ensure efficient data management by using qualitative data analysis (QDA) software such as MAXQDA (Verbi GmbH) to code and retrieve large amount of textual data to help ensure analysis rigor [49]. Doing so will help us organize, evaluate, code, annotate, and interpret qualitative data by creating easy-to-read reports and data visualizations. We will develop, program within the QDA software, and update on an as-needed basis a codebook—a list of codes, often hierarchically organized, accompanied by a description and examples of each code—to facilitate data coding. Data coders will be trained on how to use the codebook, work jointly to code approximately 20 percent of the data, and discuss any discrepancies until consensus is achieved and the codebook is appropriately adjusted.

Second, ratings of patient-centeredness collected during the EL panel process will be analyzed quantitatively to determine the existence of consensus among participants. It is recommended that every Delphi study determine how consensus will be defined among participants before the data collection begins [42]. One of the EL features is its use of the RAM [27] to automatically determine the group decision (eg, whether a particular care management strategy was deemed patient-centered) for each round 1 item, which is displayed in round 2 and is also calculated after round 3. This process, identical to that used in determining appropriateness of different DMD care management strategies, begins with determining the existence of disagreement among participants using the following a priori process. EL automatically (1) calculates the value of interpercentile range (IPR), or the range of responses that fall between the 70th and the 30th percentiles; (2) calculates the value of the interpercentile range adjusted for symmetry (IPRAS), which is a measure of dispersion for asymmetric distributions; and (3) compares the values of IPR and IPRAS to see if there is disagreement. Disagreement is said to exist if IPR>IPRAS [27,50]. Disagreement among participants automatically produces an uncertain decision. If, instead, there is no disagreement among panelists, the value of the median will determine if the group decision is positive, negative, or uncertain. If the median is within the upper tertile of the 9-point response scale (response categories 7-9), then the decision is positive, meaning that a care management approach is considered to be patient-centered. If the median is within the lower tertile of the 9-point response scale (response categories 1-3), then the decision is negative, meaning that a care management approach is considered to be not patient-centered. A median that lies within the middle tertile (response categories 4-6) produces an uncertain decision. We will use this approach to determining consensus on the patient-centeredness of care management strategies in both EL panels using round 1 and round 3 rating data.

To compare survey and modified Delphi results, we will pool the data across two EL panels and compare determinations of patient-centeredness after round 1 (survey) and round 3 (Delphi). Because there is no right or wrong response, it is not possible to determine which approach produces better results or is more valid at the time the data are collected. However, we follow a recommended practice in Delphi studies and focus on how much each method can help patients and their caregivers reach consensus [28]. To do so, we will first calculate the percentage of care management strategies for which panelists reached agreement versus those where agreement was not achieved. We will then focus on strategies where panelists reached agreement and calculate the proportion with positive, negative, and uncertain determinations. Our assumption is that there will be fewer strategies characterized by participant disagreement after round 3, which we treat as an indicator of the benefit of using the modified Delphi approach. Still, we believe the survey approach may have its own benefit. Indeed, we assume that participant attrition rates (eg, the number of nonresponders) will be smaller in round 1 than in round 3. Larger samples may help provide a better description of the diversity of patient experiences, albeit with potentially fewer qualitative details that will crystalize after round 2 discussion.

To determine the replicability of online panel ratings, we will adopt the following a priori analytic approach originally developed by Shekelle and colleagues [51] to analyze reproducibility of in-person panel ratings. We will first examine round 3 determinations of patient-centeredness for each care management strategy and identify the proportion of strategies receiving positive, negative, or uncertain determinations. Then, we will determine the pairwise percentage of agreement between the two panels and use *t* tests to identify any statistically significant differences in panel ratings. Because the distribution of ratings may be nonnormal, we will conduct sensitivity analyses using the Wilcoxon rank sum, a nonparametric method. We will treat a 70% agreement as an indicator of acceptable reproducibility, which is at least as good as that of in in-person panels [51]. Finally, we will calculate kappa coefficients comparing the determinations made by the two panels across items. If the kappa statistic is at least moderate (.41-.60), we will consider the online approach to be a reliable mode of collecting patient-centeredness ratings using the modified RAM approach [52]. This threshold is conservative; previous research shows that the reproducibility of both in-person [51] and online [31] panel findings is rarely better than moderate.

Besides comparing ratings of patient-centeredness, we will also focus on participant experiences after round 1 (survey) and round 3 (Delphi). As in earlier studies [31], we will pool the data across the two EL panels and look at the average response to each satisfaction question asked in round 1 and round 3. We will consider a mean value of 5 (agree slightly) and higher on the 7-point positively worded agreement scale to be an indicator of a generally positive opinion. Depending on sample size, we may conduct exploratory factor analyses to identify constructs that capture participant experiences and opinions about the new online system. To explore differences in participant satisfaction and perceived usefulness of the online approach after rounds 1 and 3, we will use a paired *t* test. We anticipate greater satisfaction and perceived usefulness after round 3 but a higher level of perceived participation burden.

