We will use the DCN patient registry and PPMD social media channels to recruit 20 to 25 adult patients and 60 to 70 caregivers with a range of experiences with Duchenne care and varying degrees of comfort using technology. We will then randomly assign them to two panels similar in their composition. Doing so will help us determine the replicability of panel determinations and adhere to the best practice of conducting online modified Delphi panels that suggests including 20 to 40 participants [31] to ensure their active participation while minimizing burden associated with reading comments posted by all panel members. We will recruit more than 40 participants per panel to account for attrition typical for multiround Delphi studies without face-to-face meetings. Our panels will be significantly larger than a traditional 9-person RAM clinical panel [27]. We can engage more participants because of the online nature of the panel, which helps increase the reliability of panel findings [28]. Our goal is to recruit a maximum variation sample [44] that reflects the diversity of DMD patient and caregiver experiences. This sample will not be random, because participants will be chosen on purpose to ensure their knowledge, expertise, and diversity of experiences. This is a standard approach to recruiting Delphi participants [28,45].

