In round 1, participants will use 9-point Likert scales to rate the level of patient-centeredness of selected care management strategies and explain their responses using open-text boxes provided after each rating question (Figure 1). In round 2, participants will see a distribution of responses to all round 1 questions (Figure 2). While only the panelist knows his or her individual rating, all participants know the group’s ratings. Showing statistical feedback to the participant is an essential component of the Delphi process [42]. For each question, participants will see a bar chart showing the frequency of each response category (yellow bars), a group median (blue line), their individual response (red dot), and a short statement describing the group decision based on the group agreement as produced by the RAM [27]. Consistent with best practices in Delphi studies [45], we will provide instructions on how to interpret statistical results using instructional videos and text boxes that appear when a participant hovers over a chart. Participants will be also able to review all rationale comments posted in round 1 and discuss group ratings using an asynchronous and anonymous discussion board moderated by content experts from PPMD/DCN and online engagement experts from RAND. In round 3, participants will reanswer round 1 questions and rate any new care management strategies that might have been suggested in round 2. Allowing for new questions to be added in round 3 is consistent with the best practices for conducting Delphi studies [42]. All participants will receive a $50 gift card for completing each round.

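### The survey-versus-Delphi consensus comparison is not restricted to the same raters, so a fall in disagreement may reflect who left rather than opinions converging

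*Protocol article*

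**What the plan says.** All references are to the protocol article.

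- **Comparison.** Data Analysis pools the two panels, treats round 1 as the survey and round 3 as Delphi, and compares the percentage of strategies on which agreement was reached. The stated interest is how far each method helps participants reach consensus.
- **Criterion.** The expectation is that "there will be fewer strategies characterized by participant disagreement after round 3, which we treat as an indicator of the benefit" of the modified Delphi approach.
- **Attrition.** The same paragraph assumes that "participant attrition rates (eg, the number of nonresponders) will be smaller in round 1 than in round 3". It counts this in the survey's favour: "Larger samples may help provide a better description of the diversity of patient experiences". That credit makes sense only if the round 1 results are not cut down to round 3 completers.
- **Recruitment.** Data Collection plans to "recruit 20 to 25 adult patients and 60 to 70 caregivers" and adds: "We will recruit more than 40 participants per panel to account for attrition typical for multiround Delphi studies without face-to-face meetings". No dropout rate is given.
- **Rule.** An item shows disagreement when the interpercentile range (IPR, 70th minus 30th percentile) exceeds its symmetry-adjusted counterpart (IPRAS). The rule is applied to the round 1 and the round 3 ratings, with no common set of raters defined.
- **Within-person analysis.** Only satisfaction and perceived usefulness get one, by a paired t test.

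**The concern.** Helping people reach consensus means that opinions move closer together. The quantity chosen to show it is computed on two groups that the authors themselves expect to differ. A percentile-based rule sees only the ratings submitted. If people with minority views do not return, the spread narrows just as it would had they been persuaded. Before round 3 each participant sees the group median beside their own rating, so loss related to dissent is conceivable, although the article gives no evidence for it.

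At stake is the meaning of the one stated indicator of Delphi's advantage over a survey on consensus. As specified, a fall in disagreement cannot be attributed to the discussion and feedback, and neither can the absence of a fall.

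**Working it through.** The article gives no expected disagreement or dropout figure for this comparison, so there is none to reproduce. The check asks whether dropout alone, with every rating held fixed, can change the outcome of the rule.

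**Inputs from the article.** Recruitment is 20 + 60 = 80 to 25 + 70 = 95 in total; 88 raters is used as a value in that range. The recommended panel size is 20 to 40, or 40 to 80 over two panels. Falling from 95 to 80 is a loss of 15/95 = 16%, and from 80 to 40 a loss of 50%. These figures show how much loss the design can absorb. They are not expected rates.

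**Assumption.** The article does not give the IPRAS constants. I take IPRAS = 2.35 + 1.5 × |5 − (P30 + P70)/2|, and vary the base over 2.0 to 3.0 and the factor over 1.0 to 2.0. Percentiles in the two examples use linear interpolation.

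**Example 1: spread ratings.** 88 raters, counts 6, 10, 14, 5, 5, 8, 18, 14, 8 on scores 1 to 9.
- Round 1: P30 = 3, P70 = 7, IPR = 4.0. The midpoint is 5, so IPRAS = 2.35. As 4.0 > 2.35, there is disagreement.
- 15 of the 30 raters scoring 1 to 3 leave (15/88 = 17%) and nobody changes a rating: P30 = 5, P70 = 7.4, IPR = 2.4. The midpoint is 6.2, so IPRAS = 2.35 + 1.5 × 1.2 = 4.15. As 2.4 < 4.15, there is no disagreement.
- The median moves from 6 to 7, so the determination also goes from uncertain to positive.
- The switch held for all 9 pairs of constants and all 5 percentile definitions tried.

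**Example 2: a polarised item.** 30 raters give 2 and 58 give 8.
- Round 1: IPR = 8 − 2 = 6, IPRAS = 2.35, disagreement.
- 6 low raters leave (6/88 = 7%): 24/82 = 29.3% are low, P30 = P70 = 8, IPR = 0, IPRAS = 2.35 + 1.5 × 3 = 6.85, no disagreement. Yet 29% still rate 2.
- This case is a knife-edge. If 5 low and 1 high rater leave (25 low, 57 high), P30 = 3.8, IPR = 4.2, IPRAS = 2.35 + 1.5 × 0.9 = 3.7, and disagreement remains. If the six leavers are random, the chance that all are low is C(30,6)/C(88,6) = 593,775/541,931,236 = 0.1%.

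**Simulation with fixed ratings.** 30 items, 88 raters, 2,000 runs. Item means are uniform from 4 to 7, the rater effect and the residual each have SD 2, and scores are rounded and limited to 1 to 9. Selection strength is in log-odds per SD.

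| Dropout | Who tends to leave | Items with disagreement, before → after | Runs with a fall |
|---|---|---|---|
| 20% | random | 11.6–11.7% → 13.8–14.0% | 26–27% |
| 20% | low raters, strength 0.5 | 11.3% → 11.2% | 38% |
| 20% | low raters, strength 1 | 11.6% → 8.4% | 57% |
| 20% | dissenters, strength 1 | 11.5% → 5.0% | 79% |
| 30% | dissenters, strength 1 | 11.8% → 3.9% | 83% |

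**Same raters in both rounds.** If both rounds are computed on people who rated in both, and nobody changes a rating, the two distributions are identical and the change is exactly 0. In both examples the completers already show no disagreement at round 1, so no benefit would be credited.

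**The case against.** **The comparison as deployed is legitimate.** Round 1 stands in for an engagement survey, and a survey keeps all its respondents. Comparing each mode with the people it actually retains is a fair question, participation rates are themselves compared, and the article says it cannot establish which approach gives better results. This stands, and it is why the all-rater results should be kept. It does not cover the reading of less disagreement as a sign that Delphi helped people agree.

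**Nothing shows that dissenters leave.** Participation is anonymous, only the panelist knows his or her own rating, and each completed round earns a gift card. All of this may hold them in. This also stands. A reader might infer that the bias favours the new method; the article does not support that, because it does not say who is lost, and the simulation goes either way.

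**New items.** Participants may in round 3 "rate any new care management strategies that might have been suggested in round 2", and a reader might infer that the two percentages have different denominators. Data Analysis ties the group decision to each round 1 item, recalculated after round 3, and nothing places new items in the comparison. That inference fails.

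**No confidence interval.** The comparison is a descriptive percentage in a purposive sample, and an article may leave interval methods to the full plan. Its absence is not an error.

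**Conclusion.** The concern holds in a limited form, as a should-fix. The article fixes an indicator of Delphi benefit, expects differential nonresponse in the same paragraph, and sets no common-rater analysis for ratings. The rule cannot then separate convergence from loss of dissenters.

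The possible size is material: under the assumed distributions, selective loss of 20% took disagreement from 11.5% to 5.0% of items with no opinion changed. How likely such loss is here cannot be judged from the article. Weakly selective loss left the percentage almost unchanged, and random loss raised it, so the error could also hide a real benefit. That dropout alone can move the result does not rest on the exact constants, since Example 1 held across all those tried. The percentages do rest on the assumed ratings, item number and dropout.

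**What to change.** In Data Analysis, state that:

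1. The claim that Delphi helps participants reach consensus rests on people who rated in both rounds and on the round 1 items they re-rated, with the disagreement rule applied to that same set at each round.
2. The all-rater round 1 and round 3 results are reported beside it, labelled as the survey and Delphi results as deployed.
3. The round 1 ratings of returners and non-returners are compared, for example by their distance from the group median on each item.

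Settle this before round 3 ratings are seen. It needs no new data, only linkage of each person's ratings across rounds, which the paired satisfaction test already requires. The cost is a somewhat smaller sample for the consensus claim, a result that applies to completers, and possibly a smaller apparent benefit.

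### Any fall in the number of disagreement strategies from round 1 to round 3 is read as a sign of Delphi benefit, with no allowance for re-rating noise or attrition

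*Protocol article*

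**What the plan says.** The Data Analysis section pools the two panels and compares round 1, treated as a survey, with round 3, treated as the modified Delphi result. It says that neither approach can be shown to be better or more valid when the data are collected, and proposes instead to "focus on how much each method can help patients and their caregivers reach consensus".

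The measure is simple. The team will "calculate the percentage of care management strategies for which panelists reached agreement versus those where agreement was not achieved", and will then split the agreed strategies into positive, negative and uncertain. A strategy's status comes from the spread between the 30th and 70th percentiles of its ratings: "Disagreement is said to exist if IPR>IPRAS".

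The reading is stated in advance. The authors expect to see "fewer strategies characterized by participant disagreement after round 3, which we treat as an indicator of the benefit of using the modified Delphi approach". No minimum fall and no measure of uncertainty accompanies it. The text then grants that the survey may have a benefit of its own and expects less nonresponse in round 1 than in round 3.

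Two details in Data Collection bear on the comparison. The panels are over-recruited "to account for attrition typical for multiround Delphi studies without face-to-face meetings", and strategies suggested in round 2 may be rated for the first time in round 3. For a different round 1 versus round 3 comparison the plan does name a test: "To explore differences in participant satisfaction and perceived usefulness of the online approach after rounds 1 and 3, we will use a paired" t test.

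**The concern.** Each strategy's disagreement status is a yes/no cut on a percentile range. When the same people rate the same strategy again, a strategy near the cut can change status without anyone's underlying view having moved. The net count can therefore fall for no reason other than imperfect repeatability, and the stated reading would still take that fall as a sign that feedback and discussion helped.

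Attrition adds a second source of movement. If all available raters are used in each round, round 3 rests on fewer people, so its percentiles are noisier. Those who leave may also differ in view from those who stay. Either can shift the count without any change of opinion.

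At stake is how much weight a small fall can bear as evidence that the Delphi rounds did something a survey would not have done.

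**Working it through.** The plan gives no figure for this contrast, so there is nothing to reproduce. The check asks how often the count would fall if opinions did not change between rounds.

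**Inputs from the article**
- Reading: fewer disagreement strategies at round 3, with no minimum.
- Pooled raters: the plan is to "recruit 20 to 25 adult patients and 60 to 70 caregivers", so 20 + 60 = 80 to 25 + 70 = 95.
- Disagreement: IPR above IPRAS, using the 30th and 70th percentiles.

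**Inputs not in the article (assumed)**
- Number of strategies K: 5 to 40. Data Collection still plans to ask participants about the maximum number.
- Chance d that a strategy flips in a given direction: 0.02 to 0.20.
- For the simulation: rating SD 1.5, 2.0 or 2.5; 0, 20 or 40% of strategies with two opposed camps; re-rating reliability 0.5 or 0.8; IPRAS = 2.35 + 1.5 × |5 − centre|; attrition none, or 88 raters falling to 60.

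**Step 1: sign model.** Strategies flip independently, with the same chance d in each direction. By symmetry, P(fall) = [1 − P(tie)]/2, where P(tie) = Σⱼ K!/(j! j! (K−2j)!) · d²ʲ · (1−2d)^(K−2j).

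Example with K = 10, d = 0.05: P(tie) = 0.3487 + 0.0969 + 0.0042 + 0.00004 = 0.4498, so P(fall) = (1 − 0.4498)/2 = 27.5%.

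| K | d = 0.02 | d = 0.05 | d = 0.10 | d = 0.20 |
|---|---|---|---|---|
| 5 | 8.9% | 18.6% | 28.4% | 36.0% |
| 10 | 15.5% | 27.5% | 35.3% | 40.1% |
| 20 | 24.1% | 35.0% | 39.9% | 43.0% |
| 40 | 32.5% | 39.8% | 42.9% | 45.0% |

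Conditional on exactly D flips, the chance of a fall is P(Bin(D, 0.5) > D/2): 50% for D = 1, 3 or 5, but 25% for D = 2, 31% for D = 4 and 38% for D = 10. Once ties are possible, the overall figure stays below 50%.

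**Step 2: simulation with the IPR/IPRAS criterion.** Opinions on the 9-point scale are fixed and only re-rating noise differs between rounds; K = 10, 20 or 40, with 600 runs per scenario. The simulation error is about √(0.35 × 0.65/600) = 0.019 at a rate of 35%. With 80 or 95 raters in both rounds:
- SD 1.5 to 2.0, no split opinion: a fall in about 0 to 1%. Almost no strategy shows disagreement in either round.
- SD 2.5, no split opinion: 9 to 35%. On average 0.11 to 0.81 strategies were flagged at round 1.
- SD 2.0, 20 to 40% of strategies split into two camps: 13 to 42%. On average 0.36 to 3.13 strategies were flagged.

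**Step 3: attrition.** With 88 raters at round 1 and 60 at round 3, a fall occurred in 0 to 34%. In every scenario where the count moved at all, a rise was more frequent than a fall. At K = 40, SD 2.5 and reliability 0.5, the count fell in 20.7% and rose in 50.5%, with no change in opinion.

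**The case against.** The strongest reply is that this is a descriptive expectation and not a success rule. The text calls it an assumption and an indicator, declines to rank the two methods, and credits the survey with its own advantage. Data Collection lists ratings, satisfaction and participation rates as round 1 versus round 3 comparisons, and none is named primary. Percentages are reported, so a fall of a single strategy would be visible to any reader. Where the authors want a threshold they state one, as with 70% agreement and at least moderate kappa for replicability.

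Most of that stands. A reader might infer that this contrast decides the study, or that it is a formal test with an uncontrolled type I error to be set against a conventional significance level. The article supports neither. A reader might also infer that chance yields an apparent benefit in up to half of studies. That is not supported either: 50% applies only given a fixed odd number of flips such as 1, 3 or 5, and the low end is near zero. In the attrition runs the noise worked more often against a Delphi claim than for it.

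It is also fair that a test or interval could sit in a full protocol or analysis plan that is not shown, so its absence from the article is not the point. What remains is the interpretation the article itself commits to: fewer disagreement strategies, by any amount, counts as a sign of benefit.

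Finally, the sample is purposive, so a resampling interval does not license inference to all patients and caregivers. It still shows how far the change depends on which of these participants happened to be in the panels and on how consistently they rated.

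**Conclusion.** The point holds as a minor one. The stated reading takes any fall as an indicator of Delphi benefit and makes no allowance for re-rating variability or for the attrition the plan itself expects.

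The size depends on inputs the article does not give. Across the assumed values, noise alone produces a fall in about 0 to 45% of studies: near 0% when almost no strategy shows disagreement, and roughly 10 to 45% when disagreement is more common. Where the rate is near zero, there is also almost no disagreement left to reduce, so the contrast says little in that case. With attrition the count can rise without any change of opinion, so the bare count can mislead in either direction. The lower and upper figures rest on assumed numbers of strategies, flip rates, rating spread, reliability, attrition and IPRAS constants, and should be quoted only as a sensitivity range.

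**What to change.** In the survey-versus-Delphi paragraph of Data Analysis:

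- Restrict the main comparison to strategies rated in both rounds and to participants who completed both. Strategies first rated in round 3 have no round 1 status.
- Cross-tabulate disagreement (yes/no) at round 1 against round 3, and report how many strategies moved each way.
- Give the paired difference in the percentage of strategies with disagreement, with a 95% interval from resampling participants within panel and keeping each person's two rounds together.
- Show the comparison using all raters in each round alongside, so that the effect of attrition is visible.
- Describe a fall as supporting a Delphi benefit only if the interval excludes zero in the favourable direction; otherwise report it as descriptive.

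A McNemar test across strategies should not carry the conclusion, because it treats strategies rated by the same people as independent. The interval may be coarse if few strategies start in disagreement, and that should be said.

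The cost is a change of wording and a short piece of code on data already planned for collection. The downside is that a small fall can no longer be presented as a benefit.

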Second, we will test the new approach using one of the DMD care guideline domains that was developed using RAM but without patient or caregiver input, such as cardiac or endocrine care management guidelines. To do so, we will conduct two 3-round EL panels using a modified version of the EL system to determine the level of patient-centeredness of selected DMD care recommendations already deemed clinically appropriate. Our operational definition of patient-centeredness will be informed by the existing literature and consistent with the operationalization of appropriateness used in RAM. Our 3-round design is consistent with a recommendation for conducting Delphi studies with 2 or 3 rating rounds [42]. In testing the new approach, we will compare participants’ ratings of patient-centeredness, satisfaction levels, and participation rates after rounds 1 and 3 in both panels. Because round 1 of the EL process is essentially a survey, we will treat round 1 ratings as data from a patient engagement survey—a more common mode of patient engagement than the modified Delphi approach [43]. Such a strategy is particularly relevant for comparing the two approaches in a rare disease community where the pool of potential participants is limited. Finally, as in previous studies validating the EL approach [31,39], we will determine the replicability of final panel ratings of patient-centeredness by comparing results of two EL panels conducted using the same protocol.

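### The round 1 versus round 3 participation comparison measures retention within one enrolled panel and cannot stand for survey versus Delphi participation

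*Protocol article*

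**What the plan says.** In the Protocol article, Methods, Data Collection (the second step, testing the new approach), participation is one of three outcomes to be compared: "we will compare participants’ ratings of patient-centeredness, satisfaction levels, and participation rates after rounds 1 and 3 in both panels". Round 1 supplies the survey side: "we will treat round 1 ratings as data from a patient engagement survey". The reason given is that this suits "comparing the two approaches in a rare disease community where the pool of potential participants is limited".

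The same section describes who is in round 1. The plan is "to recruit 20 to 25 adult patients and 60 to 70 caregivers", followed by: "We will then randomly assign them to two panels similar in their composition". Both panels have three rounds, and there is no survey-only group. Numbers allow for drop-out: "We will recruit more than 40 participants per panel to account for attrition typical for multiround Delphi studies without face-to-face meetings". Participants receive a $50 gift card for each round completed.

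Under Data Analysis, round 1 is labelled as the survey and round 3 as the Delphi. After saying that a survey may have an advantage of its own, the article continues: "we assume that participant attrition rates (eg, the number of nonresponders) will be smaller in round 1 than in round 3". It adds that a larger sample may describe the variety of patient experience better.

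**The concern.** A survey invitation asks for one response. The invitation in this study asks for two rating rounds and a discussion round; the pilot of the same process is put at 3 to 4 hours over 3 weeks. Someone willing to do the first but not the second declines before round 1 and is counted nowhere. Round 1 non-response is therefore that of people who had already agreed to a multi-round panel, which is a different quantity from non-response to a stand-alone survey.

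The expected result also carries little information. Losses in a panel normally build up from round to round, and the plan over-recruits for that reason. Finding more non-response in round 3 than in round 1 would mainly confirm ordinary panel attrition.

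What is at stake is one of the three stated comparisons between the two ways of engaging patients. If the result is reported as survey versus Delphi, a reader choosing between the two would take within-panel retention for a difference in reach.

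**Working it through.** **The plan's own numbers.** Recruits total 20 + 60 = 80 to 25 + 70 = 95, or 80/2 = 40 to 95/2 = 47.5 per panel. This agrees with the stated aim of more than 40 per panel, except that the low end gives exactly 40. Two things follow:

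- Round 1 cannot contain more than 80 to 95 people. That ceiling comes from panel size, which the article ties to the burden of reading other members' comments. The size of the survey sample is thus set by a Delphi constraint.
- No attrition rate is stated. The article cites 20 to 40 participants as good practice for an online panel. Attrition that leaves 20 per panel is 1 − 20/40 = 50% to 1 − 20/47.5 = 58%. Attrition that leaves 40 is 0% to 1 − 40/47.5 = 16%.

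**What is compared and what would be needed.** Define:

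- s = response to a one-off survey among people invited
- e = uptake of the three-round panel among people invited
- r1, r3 = completion of rounds 1 and 3 among people recruited

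The article names no denominator for participation. Recruited people is the one that its design implies. On that basis the plan sets r1 against r3. A survey-versus-Delphi comparison per person invited would set s against e × r3. Neither s nor e can be obtained from the planned comparison.

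**Direction.** The plan understates the survey-to-Delphi ratio when s/(e × r3) > r1/r3, that is, when s > e × r1. It understates the absolute difference when s − e × r3 > r1 − r3. These are different conditions, and the article gives none of the four rates.

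**Illustration, all rates assumed**, with r1 = 0.90 and r3 = 0.70. The plan would then show a difference of 0.20 and a ratio of 0.90/0.70 = 1.29.

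| s | e | e × r1 | e × r3 | Difference per person invited | Ratio per person invited | Plan's difference is | Plan's ratio is |
|---|---|---|---|---|---|---|---|
| 0.50 | 0.30 | 0.27 | 0.21 | 0.29 | 2.38 | too small | too small |
| 0.30 | 0.30 | 0.27 | 0.21 | 0.09 | 1.43 | too large | too small |
| 0.20 | 0.30 | 0.27 | 0.21 | −0.01 | 0.95 | too large | too large |
| 0.60 | 0.45 | 0.405 | 0.315 | 0.285 | 1.90 | too small | too small |
| 0.50 | 0.45 | 0.405 | 0.315 | 0.185 | 1.59 | too large | too small |

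A wider grid took s = 0.2, 0.3, 0.5; e = 0.15, 0.30, 0.50; and (r1, r3) = (0.9, 0.7) or (0.8, 0.5), giving 18 combinations. The plan would show a ratio of 1.29 or 1.60 and a difference of 0.20 or 0.30. Per person invited, the ratio ran from 0.57 to 6.67 and the difference from −0.15 to 0.425. The plan understated the ratio in 12 combinations and overstated it in 6. It understated the difference in 4 and overstated it in 14. These counts depend on the chosen grid and show only that both directions are possible.

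**Cumulative loss.** If only round 1 completers may enter round 3, round 3 completers cannot outnumber round 1 completers, so the expected ordering holds by construction. If round 1 nonresponders may return, the ordering is likely but not forced. The article does not say which applies.

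**The case against.** The case for the plan has real weight:

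- The choice is declared, and a reason is given. In a rare disease, a separate survey sample would use up a small pool. This is a fair reason to use the same people when comparing ratings. It does not turn round 1 completion among enrolled panellists into an estimate of survey participation.
- The sentence on attrition states an assumption and is not a test. Participation has no threshold or decision rule, unlike agreement, kappa and satisfaction. The article says that its method comparison centres on how far each approach helps participants reach consensus. This limits the consequence. Even so, participation rates are a named comparison under Data Collection, and Data Analysis reads the expected result as an advantage of surveys.
- Flow counts are commonly left to a fuller document. Their absence is not the point here. The point is the comparator and the reading, both of which the article itself fixes.

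Two stronger readings are tempting, and the document supports neither. A reader might infer that the plan necessarily understates survey reach and the participation cost of Delphi. The direction depends on rates that the article does not give and on the scale used. Recruits are chosen purposively and paid per round, so they may answer round 1 more readily than people sent a one-off survey. A reader might also infer that the expectation, in the Abstract's Conclusions, of engaging large numbers is undermined. That statement concerns the online method, and the article's own size comparison is with a nine-person clinical panel. It is not a claim to outdo surveys.

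**Conclusion.** The point holds in limited form. The planned participation comparison describes retention from round 1 to round 3 among 80 to 95 enrolled people. It cannot estimate stand-alone survey participation, and read as survey versus Delphi it may err in either direction. No single size can be given, since survey uptake, panel uptake and completion by round are all absent from the article; the figures under the working rest on assumed rates. The conclusion also assumes that recruited people are the denominator, which is inferred from the design. It does not depend on the exact denominator, because nobody is offered a survey alone. The ratings and replicability analyses are unaffected.

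**What to change.** In Data Collection and Data Analysis, describe the participation comparison as round 1 versus round 3 within one enrolled panel, and draw no survey-versus-Delphi conclusion on participation from it. The sentence that presents lower round 1 attrition as an advantage of surveys should be reworded to match.

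Report the numbers enrolled and the numbers completing rounds 1, 2 and 3, each with its denominator, and say whether round 1 nonresponders may enter later rounds. Give round 3 retention among round 1 completers as the measure of Delphi attrition.

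If counts of registry invitations are available, report them descriptively only. The article does not say that such counts exist. Purposive recruitment to a target also mixes refusal with selection, so an invited-to-enrolled ratio would not measure deterrence by the multi-round format. People recruited through social media have no comparable denominator.

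The cost is a few sentences and a small table. No extra arm, data collection or sample is needed. The downside is a narrower statement about participation.
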